## Discussion

Numerous BC patients survivors report memory troubles. A recurring complaint is that they forget what they are supposed to do at the right moment, referring to PM. This PM is essential for self-sufficiency and medical adherence and thus the well-being of BC patients. Few studies have been published on PM functioning in BC patients, and PM process impairment needs to be more precisely evaluated. Coupled with PM impairment, several BC patients report sleep disturbances. Few studies have used PSG to assess sleep in BC, but results have revealed a decrease of sleep quality in BC patients. Knowing the involvement of sleep in memory consolidation, these results support the necessity to investigate the link between memory impairment and sleep disturbances in BC. Furthermore, HT seems to have a negative impact on memory and sleep, but there is still a lack of research in this area.

The current study will assess PM using an innovating and ecological virtual reality based task. The different types of components and intentions will be distinguished and correlated with performances in various neuropsychological tests. These tests will assess working memory, episodic memory, and executive functions known to be involved in PM functioning. The findings are expected to improve understanding of PM impairment and underlying mechanism in BC patients. Sleep will be assessed by PSG in order to obtain additional information related to sleep architecture. Sleep architecture parameters will also be correlated to PM scores and performances at night-time and day-time sessions will be compared in order to put forward the consolidation of prospective memories during sleep. These various assessments will be performed among BC patients treated or not with HT and healthy women, so that it will be possible to bring to light the possible specific impact of either BC and/or HT on PM functioning and sleep quality.

Even though the current study aims at assessing PM using an ecological task in a virtual environment, it remains a limitation. Virtual reality may provoke uncomfortable sensations like nausea and dizziness. Session of familiarisation will allow participants to become accustomed with virtual reality. If at the end of the session 1, participants are not used to virtual reality and feel sick, the task will be stopped and they will be withdraw from the study.

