### Participants

The PROSOM-K study will include 25 BC patients treated with radiotherapy alone, 25 BC patients treated with radiotherapy and HT, and 25 healthy women. Patients will be recruited in Centre François Baclesse, a regional cancer centre in Caen (Normandy, France). PROSOM-K protocol will be proposed to eligible patients during a follow-up medical care with their oncologist. Healthy volunteer women, matched for age and years of education with BC patients, will be recruited from our laboratory. Once verified the eligibility criteria (see Table 1) by a physician, each participant will provide her written informed consent to be enrolled in PROSOM-K protocol.

**Table 1 Tab1:** PROSOM-K inclusion and non-inclusion criteria

	Breast cancer patients	Healthy women
Inclusion criteria	1 year post-menopausal	
	Under 70 years of age	
	At least on level 3 (end of primary schools) of the Barbizet scale	
	French native speakers	
	Treated with surgery or radiotherapy for a non-metastatic breast cancer	Normal cognitive function with the Montreal Cognitive Assessment (MOCA) score ≥ 26
	Radiotherapy completed about 6 months prior to the study	–
Non-inclusion criteria	Neurological sequelae	
	Personality disorders and progressive psychiatric disorder	
	Drug use and/or heavy drinking	
	Treated with chemotherapy	History of cancer, excepting basal-cell carcinoma and carcinoma in situ of the uterine cervix
	Patient with a paraneoplastic syndrome	–
	Patient unable to perform cognitive tests	–
	Central nervous system primitive tumour or cerebral metastases	–
	Primitive cancer different from Breast cancer	–
	Metastatic cancer	–
	Cognitive disorders pre-existing to cancer diagnosis	–

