### Statistical analysis

This study was designed to control an error risk α of 0.05 and a power of 80%. Assuming cognitive decline for 30% of BC women under HT versus 10% among healthy controls [50], the required sample size is 24 patients per group. We thus planned to enrol a total of 75 participants (25 BC patients receiving HT, 25 BC patients without indication to HT and 25 healthy women).

Descriptive statistics (relative frequency, mean value and SD) will be estimated for the socio-demographic and clinical variables from the total population included in the study. Comparison of means for sub-groups of participants will be realised by Student’s or Wilcoxon’s tests as appropriate. Comparisons of the proportions will be performed using both parametric and non-parametric tests. Link between PM and underlying cognitive functions, HT, and sleep quality, will be estimated thanks to univariate and multivariate logistic regression models, and results will be presented with odds ratios (OR) and their 95% confidence intervals (CI). All analyses will be conducted using R (version 3.4.1).

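### PM score means are compared without adjustment, so the HT contrast, between groups separated by treatment indication, is open to confounding that the planned logistic model does not address

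*Protocol article*

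**What the plan says.** All references are to the protocol article.

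- **HT objective** (Study objectives): the influence of HT on PM is to be assessed by comparing PM scores between patients with and without HT.
- **Group definition** (Statistical analysis): the study enrols "25 BC patients receiving HT, 25 BC patients without indication to HT and 25 healthy women". The groups are not randomised.
- **Matching** (Participants): "Healthy volunteer women, matched for age and years of education with BC patients". No matching of HT to no-HT patients is stated.
- **Outcome** (Outcome measures, PM task): the retrieval score runs from 0 to 54 per session.
- **Test of means** (Statistical analysis): Student's or Wilcoxon's tests, as appropriate.
- **Regression** (Statistical analysis): univariable and multivariable logistic models relate PM to HT, sleep quality and the cognitive functions behind PM, and are reported as odds ratios.
- **Inference** (Discussion): with the three groups, "it will be possible to bring to light the possible specific impact of either BC and/or HT on PM functioning and sleep quality". The only limitation discussed there is discomfort from virtual reality.

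**The concern.** HT was given or withheld for clinical reasons, so the two patient groups may differ in age, education or disease characteristics as well as in treatment. A two-sample test credits any resulting difference in PM score to HT. With 25 women per group, even a chance imbalance can be appreciable, and nothing in the stated test corrects for it.

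The article holds earlier work to this standard. In Background it sets aside a previous HT comparison partly because every patient had also received chemotherapy, so that the role of HT could not be isolated.

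In the comparison with healthy women, the factors used for matching are left out of the analysis. That costs precision in a small study.

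**Working it through.** **1. The plan's own figure.** The article states that "the required sample size is 24 patients per group", from "Assuming cognitive decline for 30% of BC women under HT versus 10% among healthy controls". For two enrolled groups, the pooled normal formula at 80% power gives 62 per group two-sided, or 49 one-sided. A value of 24 appears only if one group is set against a fixed 10% rate: (1.960×√0.09 + 0.842×√0.21)² / 0.20² = 23.7. This calculation concerns HT versus healthy women and a proportion. It gives no planning difference for HT versus no HT, and nothing below depends on it.

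**2. Detectable difference in mean score, 25 versus 25.** At two-sided 0.05 and 80% power, the normal approximation is (1.960 + 0.842) × √(2/25) = 0.79 SD. With the t distribution it is 0.81 SD.

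**3. What an unbalanced covariate could do to the HT contrast.** Suppose HT has no effect, one covariate differs by D SD between the groups, and it correlates r with PM. The spurious difference is D × r SD. The false-positive rate of the nominal 5% test follows from the shift D × r / √(2/25) (normal approximation). D and r are assumptions; the documents give neither.

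| D | r | Spurious difference (SD) | False-positive rate |
|---|---|---|---|
| 0.25 | 0.2 | 0.05 | 5.4% |
| 0.5 | 0.2 | 0.10 | 6.4% |
| 0.5 | 0.3 | 0.15 | 8.3% |
| 0.5 | 0.5 | 0.25 | 14.3% |
| 0.75 | 0.5 | 0.375 | 26.4% |

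The effect runs from negligible to serious, and the documents do not say where this trial falls.

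**4. Does the logistic model fill the gap?** Three points, set against the article's own text:

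- It needs PM as a yes/no outcome, so it does not estimate the score difference named in the objective.
- Background and Discussion say that HT may harm memory and sleep, and that episodic memory and sleep support PM. The terms named beside HT are therefore plausible mediators. Adjusting for them can remove part of an HT effect and leaves age, education and disease characteristics untouched.
- Events would be few. At the planning rate the HT group yields 25 × 0.30 = 7.5. If the no-HT rate is 10-30% (assumed), that group yields 2.5-7.5. The total is 10-15 among 50 patients, too few for several covariates.

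**5. Precision from using the matching factors.** If age and education explain a share R² of PM variance, the detectable difference becomes 0.81 × √(1 − R²), and the gain is worth 1/(1 − R²) times the sample. R² is assumed.

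| R² | Detectable difference (SD) | Equivalent sample |
|---|---|---|
| 0.08 | 0.78 | ×1.09 |
| 0.15 | 0.75 | ×1.18 |
| 0.30 | 0.68 | ×1.43 |

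The first row corresponds to two uncorrelated factors, each with r = 0.2 (2 × 0.2² = 0.08).

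**The case against.** The strongest reply is that the tests of means are not the whole plan: a multivariable model containing HT is stated, and a condensed article may leave its covariate list to a fuller document. This is right as far as it goes. A reader might infer that the HT analysis as a whole is unadjusted, and the text does not support that. The reply does not rescue the score comparison, because the test fixed for means admits no covariates and the regression that is named has a different outcome and names likely mediators.

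Eligibility also narrows the scope for imbalance. All patients are post-menopausal, within an upper age limit of about 70, non-metastatic, untreated with chemotherapy, and about 6 months past radiotherapy. This stands, and it makes the interval since radiotherapy a weak candidate confounder.

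The Discussion speaks only of a possible impact, so it would be unfair to say that a specific HT effect is promised. It still presents the three-group design as able to bring such an effect to light, with no caveat about how the groups arise.

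Two further inferences are tempting and unsupported. The article does not say that age and education determine PM; it uses them only for matching, and the factors it names as affecting PM are depression, stress, anxiety and fatigue. Nor can one conclude that 25 controls cannot be matched to both patient groups: the text does not say whether matching is individual, and frequency matching to all patients fits it equally well.

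Finally, covariate adjustment does not remove confounding by indication. This also stands. It is a reason to change the wording as well as the model.

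**Conclusion.** The point holds in a limited form. The stated comparison of PM score means is unadjusted, the HT and no-HT groups are separated by indication with no stated matching between them, and the logistic model does not supply an adjusted comparison of the scores. The HT contrast is therefore open to confounding. To say that it is confounded would go further than the documents allow, since they give no covariate differences or correlations; the bias figures above are illustrations only.

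Because the comparison group is defined as "25 BC patients without indication to HT", indication and treatment coincide between the two patient groups. No regression within this design can fully separate them, so the result can be read only as an association.

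For patients versus healthy women, matching already deals with age and education as sources of bias. What remains is mainly lost precision: 0.81 against 0.75-0.68 SD if the two factors explain 15-30% of variance, and a smaller gain if they explain less.

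**What to change.** - **Model.** Replace the two-sample tests of PM scores by one linear model of the score on group (three levels), age and years of education, and take all three group contrasts from it. Age and education are already needed for matching.
- **HT versus no HT.** Add tumour stage where it is recorded, fitting this version in the 50 patients. Leave cognitive test scores and sleep measures out of the model for the total HT effect. Analyses that include them can stay, labelled as exploring mechanism.
- **Wording.** In Study objectives and Discussion, describe the HT result as an association among women selected by indication, and name confounding by indication as a limitation.

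The cost is small. With 75 women, the two covariates reduce the residual degrees of freedom from 72 to 70. In the 50 patients, age, education and a single term for stage reduce them from 48 to 45. No further women or visits are required, and the HT conclusion becomes more modest.

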## Conclusion

The PROSOM-K trial is expected to bring multifaceted information on PM difficulties among BC patients. Indeed, the assessment of the relationship between components and intentions of PM using virtual reality, and neuropsychological tests, should lead to advanced knowledge about the PM processes impaired in BC patients. PSG data will be an opportunity to better explore the architectural sleep disturbances in BC. Thanks to the three groups of participants and the three sessions, some information should be given on the influence of sleep and HT on PM functioning. In a longer term, we expect our findings will be useful for patients and clinicians to understand and take into account their complaints, and thereby improve their take care. We also expect our results will further help to develop applications to improve their daily life and compensate for their PM impairment, as well as to improve cognitive therapy related to sleep and cognitive disorders.

## Abbreviations

BC: Breast Cancer
EB: Event-Based
HT: Hormonal Therapy
PM: Prospective Memory
PSG: Polysomnography
TB: Time-Based
